### Diffusion data analysis

All diffusion data are preprocessed offline using FSL 5.0.9 (https://fsl.fmrib.ox.ac.uk/fsl/fslwiki/FSL) (58). Preprocessing included correction for subject motion and eddy currents, with the b-matrix adjusted to account for rotational motion. Diffusion tensors are then estimated using nonlinear least squares fitting. Whole-brain tractography is conducted with a 2-mm uniform seed point resolution, applying termination criteria of FA < 0.2, angle < 30°, and fiber length < 50 mm.

The mean fractional anisotropy (FA) of the FAT is extracted to evaluate its microstructural integrity. FA reflects the directional dependency of water diffusion within fiber tracts, with values ranging between 0 (representing isotropic diffusion) and 1 (representing diffusion along a single direction), with higher values indicating greater fiber coherence and organization. FA is considered sensitive to microstructural properties such as myelination and axonal density, making it a useful marker for detecting subtle changes in white matter (59). FA values of the FAT are analyzed using a two-way mixed-design repeated-measures ANOVA, with group (active vs. sham) as a between-subject factor and time (pre- vs. post-treatment) as a within-subject factor. *Post hoc* pairwise comparisons receive Bonferroni correction. To assess structure–function–behavior relationships, correlations are computed between FA changes, FC alterations, and behavioral improvements using Pearson correlation analyses, with *p*-values FDR-corrected for multiple comparisons (*p* < 0.05).

### Safety

Adverse effects are defined as any negative experiences experienced by participants during iTBS or MRI procedures. Investigators will record all adverse events occurring during treatment and up to 1 week afterward. Seizures, the most severe TMS-related adverse events with an estimated risk of 0.02%, are expected only during or immediately following iTBS. MRI-related side effects will be reported within 24 hours, with ear protection provided to limit acoustic disturbance. Any serious incidents will be promptly reported to the Medical Research Ethics Committee of Wuxi Central Rehabilitation Hospital.

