**Methods:**

In this single-center, randomized, double-blind, sham-controlled trial, 40 participants with early subacute PSA (1–3 months post-stroke) are allocated to receive either active or sham iTBS targeting the left or right pre-SMA, localized via individualized MRI mapping. Participants will undergo a 2-week intervention, with language and neuroimaging assessments conducted at baseline, immediately post-intervention, and at a 1-month follow-up. Primary outcome measures are the Western Aphasia Battery (WAB). Second outcomes measures will be including the Boston Naming Test (BNT), the Boston Diagnostic Aphasia Examination (BDAE), non-language cognitive assessment (NLCA), alongside functional connectivity analysis from resting-state fMRI.

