The iTBS will be delivered via a Magneuro 100 magnetic stimulation device (Vishee Medical Technology Co., Ltd., Nanjing, China), equipped with a figure-eight stimulation coil (70 mm diameter) and integrated with a neuronavigational system (Visor 2, ANT Neuro, Netherlands), using a figure-of-eight coil capable of delivering both active and sham stimulation. The rTMS was conducted to stimulate the area over the primary motor cortex (M1) of the unaffected hemisphere (50). The RMT was defined as the minimum stimulus intensity that produced a motor evoked potential (MEP) response of at least 50 μV peak-to-peak amplitude in five out of ten trials in the abductor pollicis brevis muscle of the unaffected side (51). Following this determination, participants will undergo iTBS, delivered either as active stimulation in the experimental group or as sham stimulation in the control group. The iTBS protocol comprises three sets of 600 pulses delivered daily, with each set lasting 200 s at 15-min intervals. This results in a total of 1,800 pulses per day, which are targeted at the personalized pre-SMA. iTBS will then be delivered at 80% of the individual's rMT over the pre SMA. This intensity is based on literature demonstrating the safety and efficacy of 80% rMT stimulation applied to the superior frontal gyrus in patients with post stroke aphasia, and has been shown to induce consistent excitatory effects relevant to language recovery (8). The intervention will be delivered 5 days per week over 2 weeks, totaling 10 sessions per participant. The choice of a 15-min intersession interval was based on evidence from accelerated iTBS studies demonstrating that shorter spacing between sessions maintains safety and efficacy comparable to conventional 1-h intervals while improving clinical feasibility (52–54). All TMS operators will complete standardized training and assessment prior to the trial to ensure consistency. To ensure procedural consistency, each participant will receive all treatments from a single assigned TMS operator. Following iTBS treatment, a certified speech-language therapist will administer a 30-min session of SLT for each participant.

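### The definition of adverse effects is narrower than the recording window, and routine recording ends near Day 21 although participants are assessed at Day 44

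*Protocol article*

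**What the plan says.** Four statements in the Safety section of the protocol article bear on this.

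- The definition: "Adverse effects are defined as any negative experiences experienced by participants during iTBS or MRI procedures".
- The recording rule, in the next sentence: "Investigators will record all adverse events occurring during treatment and up to 1 week afterward".
- The most severe TMS-related event: seizures "are expected only during or immediately following iTBS".
- Serious events: "Any serious incidents will be promptly reported to the Medical Research Ethics Committee of Wuxi Central Rehabilitation Hospital". No end date is attached to this duty.

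The Treatment section fixes the length of treatment: "The intervention will be delivered 5 days per week over 2 weeks, totaling 10 sessions per participant". The abstract places the assessments at baseline, "immediately post-intervention, and at a 1-month follow-up". Table 1 puts the post-intervention visit at Day 14 (±3 days) and the follow-up visit at Day 44 (±3 days), and ticks WAB, BDAE, BNT and NLCA at both. It has no row for adverse events.

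**The concern.** There are two separate points.

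The first is scope. A headache on the evening after a session did not occur during a procedure, so it falls outside the definition, yet it falls inside the recording window. A seizure just after the last pulse train is in the same position, although the section treats seizure as its gravest risk. *Adverse effects* is the only term the section defines. *Adverse events*, *side effects* and *serious incidents* are then used without definition, so a reader of the results could not be sure what a reported count contains.

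The second is duration. Language outcomes are followed to Day 44, but routine adverse event recording stops about three weeks before that. Benefit and harm would be described over different periods, in patients who are only one to three months past a stroke at entry. What is at stake is safety information in both arms, which could be had at a visit that takes place anyway.

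**Working it through.** **Scope: the statements side by side (Safety section)**

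| Statement | Time covered |
|---|---|
| Definition of adverse effects | During iTBS or MRI procedures |
| Recording of adverse events | Treatment period plus 1 week |
| Expected timing of seizures | During iTBS or immediately after it |
| Reporting of serious incidents | No end stated |

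The first row is narrower than each of the other three.

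**Duration: inputs**

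- End of treatment, E: taken as the day of the post-intervention visit, nominally Day 14, range Day 11 to 17 (Table 1). This is an assumption. It agrees with ten sessions over two weeks (Treatment section).
- Follow-up visit, F: nominally Day 44, range Day 41 to 47 (Table 1).
- Recording window after treatment: 7 days (Safety section).

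**The plan's own figure.** F − E = 44 − 14 = 30 days, which reproduces the 1-month follow-up given in the abstract.

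**Nominal result.** Recording closes at E + 7 = 14 + 7 = Day 21. Days outside it: F − (E + 7) = 44 − 21 = 23. Share of post-treatment follow-up: 23/30 = 76.7%.

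**Range over the visit windows.** The share is (F − E − 7)/(F − E).

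| E | Recording closes | F | Days outside | Post-treatment days | Share |
|---|---|---|---|---|---|
| 17 | Day 24 | 41 | 17 | 24 | 70.8% |
| 14 | Day 21 | 44 | 23 | 30 | 76.7% |
| 11 | Day 18 | 47 | 29 | 36 | 80.6% |

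The first and last rows are the extremes, so the share runs from 71% to 81%.

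**Sensitivity to the denominator.** Counted from Day 0, the nominal share is 23/44 = 52.3%, with extremes of 17/41 = 41.5% and 29/47 = 61.7%. On that basis a statement that more than half is uncovered does not hold throughout the windows. Treatment days are covered by the recording rule, so the post-treatment period is the better denominator, and on it the statement holds throughout.

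**The case against.** The strongest reply is that the two sentences use different terms and can both be followed. Investigators record all adverse events in the window, and those that arise during a procedure form the narrower class of adverse effects. The definition does not say that adverse effects occur *only* during procedures, and the recording instruction itself is clear. This stands in part: the mismatch is loose terminology rather than a proven contradiction in what will be collected. It does not remove the need to reconcile the text, because the wider term is left undefined and the definition misses the immediate post-stimulation period in which the section itself expects seizures.

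A second reply is that treatment plus one week is a stated and defensible choice, given when seizures are expected. That reasoning is offered for seizures alone, whereas the window applies to all adverse events. Still, nothing in the article says that stimulation-related events are expected later than a week, so extending the window is an improvement on a design choice and not the correction of an error.

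Three stronger readings are tempting, and the documents do not support them.

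- A reader might infer that the window cannot be observed because no visit falls near Day 21. Recording to one week needs no visit. Calls or care records would serve, and an article may leave the method to the full protocol.
- A reader might infer that the period after Day 21 goes unobserved. Participants are assessed at Day 44, and the duty to report serious incidents has no stated end. What stops is routine recording.
- A reader might infer a biased safety comparison of active against sham. The article specifies no such comparison, and the window is the same in both arms. The loss is of information, and no differential bias is shown.

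**Conclusion.** The point holds in two parts. The definition of adverse effects does not match the recording window or the stated timing of seizures, and the passages must be reconciled. Routine recording also ends at about Day 21, leaving 23 of 30 post-treatment days outside it (71-81% across the visit windows), although participants are assessed at Day 44.

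The figures assume that treatment ends on the day of the post-intervention visit and that both visits stay within the ±3 days of Table 1. They describe routine recording only. How many events would be missed cannot be estimated, because the article gives no event rates for that period other than a general seizure risk of 0.02%. Reconciling the definition is the firmer part of the recommendation. The longer window is more discretionary, but cheap.

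**What to change.** In the Safety section, use one definition: any untoward event from the first session onward, in both arms, with events during iTBS or MRI procedures flagged as a subset. Use one term for it throughout. Extend routine recording to the Day 44 visit, and have blinded assessors put a prompted question at T1 and again at Day 44. Add an adverse event row to Table 1.

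No extra visit is needed, and outcome assessors are already blinded under the Blinding section. With recording to Day 44, no post-treatment days up to that visit would lie outside the window.

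There are two costs. Some events unrelated to stimulation will be recorded, which the procedure flag helps to separate. Recall over about a month is also imperfect, the more so because every participant has non-fluent aphasia, so a prompted question will not capture everything.

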## Discussion

This randomized controlled clinical trial with a sham intervention aims to explore the neural and behavioral effects of personalized iTBS targeting the ipsilesional or contralesional pre-SMA. We hypothesize that stimulating the personalized pre-SMA with iTBS can enhance the effects of SLT on language recovery in PSA by modulating pre-SMA functional connectivity and inducing microstructural changes in the FAT, both of which are involved in language processing. The findings may offer evidence supporting the pre-SMA as a potential optimal stimulation target for treating subacute PSA. This study is designed to ascertain the integrity of the lesion-side FAT guided by DTI, and to carry out personalized intervention based on this. It is found that personalized pre-SMA iTBS stimulation might be a new neuromodulation approach for PSA recovery, as it is associated with the recovery of aphasia. Several studies indicate that rTMS has emerged as a potential therapeutic tool for ameliorating language dysfunction associated with PSA, yet the heterogeneity of treatment outcomes remains relatively high, which is attributed to variations in therapeutic targeting (60, 61). An extensive body of evidence indicates that the pre-SMA, as a specific target, is linked to the recovery process in patients with PSA, which further implies that it may serve as a potential stimulation target for cranial magnetic stimulation CMS interventions in PSA treatment (10). The development of fMRI-guided TMS-based personalized targeting for research may improve the therapeutic efficacy and therapeutic response rate of neuromodulation techniques, become an emerging means of stroke treatment, and be able to effectively reduce the burden of stroke patients' families and save social resources (62).

The correlation between the increased efficacy of fMRI-based individualized targeting in the recovery of speech function in PSA and the mechanism of neural remodeling has not yet been explored: Prior studies document that the pre-SMA serves as a key node in the reorganization of the neural speech network and neural cognitive network in patients with PSA (63), and our preliminary experiments confirm the important role of the pre-SMA in the recovery of speech function in patients with PSA, as demonstrated by the resting-state fMRI-functional connectivity analyses. which exerts a crucial role in the process of speech function recovery, laying a scientific foundation for the clinical research of this project. This project is to explore the efficacy of fMRI-based individualized targeting in enhancing the language recovery for PSA, and then to provide a basis for decision-making on individualized TMS treatments for PSA.

## Limitation

The current study presents several limitations that warrant consideration. First, the recruitment of participants with PSA remains challenging, resulting in relatively small sample sizes in many studies. This limitation compromises statistical power and consequently restricts the reliability and generalizability of research findings. Future studies with larger cohorts will incorporate aphasia subtype-based stratification to better capture potential differential responses across aphasia phenotypes. Furthermore, the absence of long-term follow-up in this investigation confines our observations to short-term therapeutic outcomes, thereby hindering a comprehensive understanding of treatment efficacy in sustained recovery processes. This methodological gap may obscure the longitudinal trajectory of therapeutic interventions.

Additionally, substantial heterogeneity exists within the PSA population regarding lesion topography, infarct volume, aphasia subtypes (e.g., Broca's aphasia, Wernicke's aphasia), and severity stratification (64). Such clinical variability complicates comparative effectiveness analyses across studies, as differential treatment responses among patients may substantially influence outcome interpretation. The inherent neurobiological diversity in this population necessitates cautious generalization of therapeutic outcomes. Perfusion imaging such as ASL was not included in the current protocol. Future studies should integrate cerebral blood flow measurements to better capture hemodynamic contributions to language recovery.

Lastly, although the pre-SMA also participates in motor control and planning, this protocol prioritizes language-related outcome measures to specifically evaluate speech network modulation. Including motor assessments such as the Fugl–Meyer or ARAT will be considered in subsequent studies to further disentangle motor- and language-specific contributions to recovery mechanisms.
